#### Secondary

All variables will be examined using descriptive statistics to ensure they meet the assumptions necessary for parametric analysis. If not, non-parametric equivalent analyses will be used. Repeated measures ANOVA with planned comparisons will examine between group differences in the secondary outcome variables and investigate the effects of the intervention.

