### Power calculation and sample size

The primary dependent variable of falls frequency over 12 months was used to determine sample size. Based on previous studies [8,52] and setting power at 80%, alpha at 5% and with a drop-out rate of 20%, a sample size of 90 is required in each group to detect a clinically significant difference of 25% reduction in falls frequency in the intervention group. This sample size will also be sufficient to identify between-group differences in the secondary outcomes of the Movement Disorders Society – Unified Parkinson’s Disease Rating Scale (MDS-UPDRS) [53] and Parkinson’s Disease Questionnaire-39 items (PDQ-39) [54,55].

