### Assessments

All assessments will be performed in the participant’s home by a trained physiotherapist blind to group allocation. Participants will be reminded not to disclose their treatment or group allocation to the assessor. Assessments will occur in the week prior to therapy commencing (T1), in the week after six weeks’ therapy (T2) and 12 months after therapy completion (T3). Difference between T1 – T2 assessments will allow evaluation of the immediate effect of therapy, while T2 to T3 difference will determine whether the IR program has a longer term effect. Each assessment will include the MDS-UPDRS [53], PDQ39 [54,55] and the EuroQol EQ-5D^TM^[58]. Medications and their dosage will be recorded on each test occasion.

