#### Secondary

Secondary outcome measures include changes in motor disability, global disability and quality of life. Changes in motor disability and global disability will be compared from pre- to post-therapy (T1 to T2) and from T2 to 12 months after therapy ceases (T3), using respectively the motor section III of the MDS-UPDRS [53,61] and the full MDS-UPDRS. The MDS-UPDRS is the current version of the original UPDRS [62], augmented and revised in line with the findings of its review taskforce (MDS, 2003), and represents the gold standard in PD assessment. Quality of life will be evaluated on the same occasions, using the disease-specific PDQ-39 [54,55] which has demonstrated validity, reliability and sensitivity. The widely used generic EQ-5D [58] will allow comparison of quality of life with non-PD populations [63].

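### The immediate effect on disability and quality of life is tested as an unadjusted T1-to-T2 change; adjusting for the T1 score would be more precise at almost no cost

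*Protocol article*

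**What the plan says.** Under Assessments, the baseline is taken before treatment: "Assessments will occur in the week prior to therapy commencing (T1"). T2 follows the six weeks of therapy and T3 comes 12 months after therapy ends. "Each assessment will include the MDS-UPDRS [53], PDQ39 [54,55] and the EuroQol EQ-5D", so every secondary scale has a T1 score. The same section fixes the role of that score: "Difference between T1 – T2 assessments will allow evaluation of the immediate effect of therapy". The T2-to-T3 difference is assigned to the longer-term effect.

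Under Outcome measures, Secondary, the wording is again about change: "Changes in motor disability and global disability will be compared from pre- to post-therapy (T1 to T2") and then from T2 to T3, using MDS-UPDRS Part III and the full scale. For PDQ-39, "Quality of life will be evaluated on the same occasions".

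Under Statistical analysis, Secondary, the model is named: "Repeated measures ANOVA with planned comparisons will examine between group differences in the secondary outcome variables and investigate the effects of the intervention". If parametric assumptions fail, "If not, non-parametric equivalent analyses will be used". No covariate is mentioned.

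Under Power calculation and sample size, the protocol says of MDS-UPDRS and PDQ-39: "This sample size will also be sufficient to identify between-group differences in the secondary outcomes". It gives no effect size, standard deviation or correlation for them.

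**The concern.** A pre-treatment score can enter the analysis as a response or as a covariate. Here it is a response. In a two-group repeated measures ANOVA, the group-by-time contrast between T1 and T2 is the difference between the arms in mean change. That fixes the slope of T2 on T1 at 1 and does not estimate it. When the true slope is below 1, which is usual for scores measured with error, subtracting the whole of T1 adds noise.

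Two things are at stake. The first is precision for MDS-UPDRS Part III, MDS-UPDRS total, PDQ-39 and EQ-5D. The second is how the result behaves when the arms differ by chance at T1. Randomisation is stratified by referral source only, so balance on baseline severity is left to chance. An arm that starts worse will tend to show more improvement through regression to the mean, and a change score credits that to treatment.

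**Working it through.** **Inputs from the protocol.** 90 per group, 20% drop-out, alpha 5%, power 80% (Power calculation and sample size). Completers: 90 x 0.8 = 72 per group. There is no stated figure for the secondary outcomes to reproduce. The 90 per group was set for falls frequency, and this point does not depend on how it was reached.

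**Assumptions.** Two-sided test, complete T1 and T2 data, equal standard deviation (SD) at T1 and T2, normal approximation. The T1-T2 correlation rho is not in the document and is varied.

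**Step 1: variance.** Per arm, in units of SD squared:
- change score: 2(1-rho)
- T2 adjusted for T1: 1-rho² = (1-rho)(1+rho)
- ratio, adjusted to change: (1+rho)/2, which is below 1 for every rho below 1

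**Step 2: power.** An effect with 80% power under change scores has a standardised size of 1.960 + 0.842 = 2.802. Adjustment multiplies this by sqrt(2/(1+rho)). Power is the normal probability below the result minus 1.960.

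| rho | variance ratio | variance cut | standardised effect | power, change | power, adjusted |
|---|---|---|---|---|---|
| 0.5 | 0.75 | 25% | 3.235 | 80% | 90% |
| 0.7 | 0.85 | 15% | 3.039 | 80% | 86% |
| 0.8 | 0.90 | 10% | 2.953 | 80% | 84% |
| 0.9 | 0.95 | 5% | 2.874 | 80% | 82% |

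The variance cut is also the percentage fewer patients needed for equal power. Holding the effect at an assumed 0.4 SD instead, with 72 per group, power goes from 67% to 79% at rho 0.5, from 87% to 92% at 0.7, and from 97% to 98% at 0.8.

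**Step 3: chance imbalance.** If the arms differ at T1 by b, the expected difference at T2 with no treatment effect is rho x b. The expected difference in change is therefore rho x b - b = -(1-rho) x b. With 72 per group, one standard error of the T1 difference is sqrt(2/72) = 0.167 SD.

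| rho | shift at 1 SE (0.167 SD) | shift at 1.96 SE (0.327 SD) |
|---|---|---|
| 0.5 | 0.083 SD | 0.163 SD |
| 0.7 | 0.050 SD | 0.098 SD |
| 0.8 | 0.033 SD | 0.065 SD |

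**Step 4: simulation, 20,000 trials per rho, no treatment effect.** At rho 0.5, 0.7 and 0.8:
- variance ratio: 0.760, 0.866 and 0.903, close to the formula
- all trials: the mean change-score error was zero to two decimals, with rejection in 5.0%, 4.7% and 4.9%
- only trials whose T1 imbalance exceeded 1 SE: change scores were off by 0.13, 0.07 and 0.05 SD and rejected in 9.8%, 6.7% and 6.8%; the adjusted analysis was off by less than 0.005 SD and rejected in 5.6%, 4.9% and 5.3%

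**The case against.** The strongest reply is that this is a condensed article. Its one sentence on the model does not exclude covariates, and a comparison of changes is compatible with adjustment: regressing change on group and T1 gives the same group effect as regressing T2 on group and T1. This stands in part. The absence of recruitment source from the model is not counted here as an error, since a covariate list is commonly left to the analysis plan. The role of T1 is different. The article states both the contrast (T1-to-T2 difference) and the model family (repeated measures ANOVA), and as normally run that combination makes T1 a response. That is a stated choice, not an omitted detail.

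It is also fair that the gain depends on a correlation the document does not give. T1 and T2 are about seven weeks apart in a chronic disease, so a high rho is possible. At 0.8 to 0.9 the gain is only 2 to 4 points of power.

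A reader might infer more than the text supports:
- *That the planned analysis is biased.* It is not. Over all randomisations the change-score comparison averages zero error with the correct alpha. The shift in Step 3 is conditional on the imbalance that happens to occur.
- *That the ANOVA's group main effect over T1 to T3 will be read as the treatment effect*, which would dilute it with a visit before treatment. Nowhere is this said. The protocol specifies planned comparisons and defines the T1-T2 and T2-T3 intervals.
- *That the sample is too small for the secondary outcomes.* With no effect size or SD stated, nothing shows this. The calculation shows only that another analysis of the same data is more efficient.

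**Conclusion.** The point holds as a matter of efficiency. The stated analysis of the immediate effect is valid but discards precision that the T1 data already provide. The loss is moderate at rho 0.5 to 0.7 (10 to 6 points of power, from a base of 80%) and small at 0.8 to 0.9 (4 to 2 points). The gain from adjusting is positive at every rho below 1, apart from the negligible cost of the extra parameters. Protection against a chance T1 imbalance is a second benefit, of size (1-rho) times that imbalance.

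The figures rest on 72 completers per group, equal SDs at T1 and T2, and assumed correlations. They concern the secondary outcomes only. The change is worth making before unblinding because it is nearly free, but nothing here invalidates the plan.

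**What to change.** In Outcome measures (Secondary) and Statistical analysis (Secondary), state that the immediate effect on each of MDS-UPDRS Part III, MDS-UPDRS total, PDQ-39 and EQ-5D is the between-group difference at T2. Estimate it from a linear model with the T2 score as response and treatment group, the T1 score of the same measure and recruitment source (the randomisation stratum) as terms. Mean changes can still be shown descriptively.

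If a between-group difference at T3 is also reported, adjust it for T1 in the same way. That would be in addition to the T2-to-T3 contrast the protocol defines, not a replacement, because the two estimate different things.

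The cost is a change of wording and a few degrees of freedom: one for T1, and one fewer than the number of recruitment sources. No extra patients, visits or data are needed.

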## Methods/design

### Design

This study will be a prospective controlled trial with random allocation stratified by recruitment source to control for possible bias. Intention to treat analysis will be used and assessors blinded to group allocation. A concurrent economic analysis will evaluate the costs of falls and their management, as well as the costs of implementing the therapy intervention.

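### Repeated measures ANOVA over T1, T2 and T3 sits badly with intention to treat when 20% drop-out is allowed for; a mixed model using all available visits would serve the secondary outcomes better

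*Protocol article*

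**What the plan says.** The Secondary part of the Statistical analysis section names the method: "Repeated measures ANOVA with planned comparisons will examine between group differences in the secondary outcome variables". Before that, the variables are to be screened descriptively against the assumptions for parametric analysis, and "If not, non-parametric equivalent analyses will be used". Those alternatives are not named.

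Other sections bear on this choice:

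- Assessments sets three visits: T1 in the week before therapy, T2 in the week after the six-week program, and T3 at 12 months after therapy. The secondary Outcome measures section compares change from T1 to T2 and from T2 to T3.
- Design commits to the analysis principle: "Intention to treat analysis will be used".
- Power calculation and sample size works from falls frequency: "setting power at 80%, alpha at 5% and with a drop-out rate of 20%, a sample size of 90 is required in each group". It adds: "This sample size will also be sufficient to identify between-group differences in the secondary outcomes".
- For falls, the Primary part of the Statistical analysis section chooses negative binomial regression because it can accommodate unequal follow-up. No comparable feature is claimed for the secondary method.

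**The concern.** Classical repeated measures ANOVA needs a full row of T1, T2 and T3 for each person. Unless missing values are imputed, a person who misses T3 is removed from every contrast, including T1 to T2, for which the data are in hand. With a year between T2 and T3, T3 is the visit most likely to be missed.

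Two things are at stake for the MDS-UPDRS, PDQ-39 and EQ-5D. The first is precision at T2, which would be given up without need. The second is validity: the T2 comparison would be made in people selected by an event after T2, and if that selection works differently in the two arms the randomised comparison is distorted.

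The fallback adds a further loose end. Because it is unnamed and triggered by looking at the data, the test finally used, and the quantity it addresses, are open until after inspection.

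**Working it through.** **Inputs from the protocol article.** 180 randomised, 90 per group; drop-out allowance 20%; power 80%; alpha 5% (taken here as two-sided, which the article does not state); three visits. Everything else below is an assumption and is marked as such.

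**The plan's own figure.** 72 / (1 − 0.20) = 90, so 90 per group corresponds to 72 completers per group. The 72 itself cannot be reproduced, because no control rate, SD or dispersion is given. Only the drop-out step can be checked, and it is consistent.

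**People and variance at T2.** Assume the 20% applies to T3 visits.

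- Excluded from a three-visit complete-case analysis: 180 × 0.20 = 36. Retained: 144.
- If a fraction f of the 36 were seen at T2, then 144 + 36f people have T2 data, and the variance ratio of complete-case to all-available is (144 + 36f)/144 = 1 + 0.25f.
- f = 0 gives 1.00; f = 0.5 gives 1.125; f = 1 gives 1.25.
- With 10% loss instead of 20%, and f = 1, the ratio is 180/162 = 1.11.

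So 1.25 is a ceiling at 20% loss.

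**What this means for power at T2.** For two equal groups, the detectable standardised difference is (1.96 + 0.842) × √(2/n).

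- n = 90: 2.802 × 0.1491 = 0.42 SD.
- n = 72: 2.802 × 0.1667 = 0.47 SD.
- Power at n = 72 for the difference detectable at n = 90: Φ(0.4176/0.1667 − 1.96) = Φ(0.55) = 71%, against 80%.

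This loss is avoidable only at T2. At T3 the missing values are missing under any method, and the sample size already allows for that.

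**Bias, by illustrative simulation.** Assumptions: 90 per group, unit variance, correlation 0.6 between visits, a true effect of −0.40 SD at both T2 and T3, about 18% missing T3 with probability depending on the T2 value, 4,000 repetitions. The true T1–T2 contrast is −0.40 and the true T2–T3 contrast is 0.

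| Drop-out pattern | T1–T2, completers | T1–T2, all data | T2–T3, completers | T2–T3, using all data |
|---|---|---|---|---|
| Same in both arms | −0.38 | −0.40 | −0.01 | 0.00 |
| Opposite in the two arms | −0.52 | −0.40 | +0.12 | −0.01 |

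The completer-only error is about 0.02 SD in the first case and 0.12 SD in the second. The standard deviation of the T1–T2 estimate was 0.148 in completers against 0.134 with all data when the pattern was the same in both arms. That is a variance ratio of (0.148/0.134)² = 1.22, in line with 180/147.4 = 1.22 for the average of 147.4 completers.

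**Fallback.** The Friedman test, the direct rank analogue of a one-group repeated measures ANOVA, ranks visits within a person and does not use group, so it does not test group-by-time. A Mann-Whitney test on change scores compares the groups on one interval. Simulated with 72 per group and correlation 0.6, it had size 0.042 and 73% power for a 0.40 SD group difference in change.

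**The case against.** The strongest reply is that the article names a method and does not say that incomplete participants are dropped. Imputation and analysis sets may be set out in a full protocol or analysis plan that is not shown, and repeated measures ANOVA on imputed data would keep all 180. This stands as far as it goes. A reader might infer that the plan contradicts its intention-to-treat commitment, but the text supports only a tension. What remains is that the model class is fixed here, and without imputation it is one that cannot use an incomplete record.

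Other stronger readings also fail:

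- **That the fallback cannot test the group-by-time effect.** The article does not name Friedman, and its contrasts are changes over two intervals. With two groups, a Mann-Whitney test on each change score addresses them. The fair criticism is that the fallback is unnamed and data-driven.
- **That unequal spacing of visits breaks the analysis through sphericity.** A planned contrast with one degree of freedom and its own error term is a t-test on change and needs no sphericity.
- **That 36 people will be lost.** The 20% is an allowance in a falls calculation, not a forecast of missed visits.
- **That bias is established.** It was negligible with matching drop-out patterns. Opposite patterns are possible, since strength training and discussion sessions differ in kind, but contact time is matched and nothing in the article shows that they will occur.

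**Conclusion.** The point holds as a poor choice of method for the secondary outcomes, not as an explicit contradiction. Run in its classical form without imputation, the stated ANOVA would discard T2 data already collected and fit poorly with intention to treat. The size is moderate: at most 36 of 180 people excluded and 1.25 times the necessary variance at T2, if the 20% allowance applied to T3 and all those people were seen at T2. Bias is likely small if drop-out patterns match across arms; it reached about 0.12 SD under opposite patterns, on assumed inputs. The fallback should be settled in advance. The primary falls analysis, which adjusts for varying follow-up, is untouched. The change is worth making because it costs little.

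**What to change.** Replace the repeated measures ANOVA with a likelihood-based mixed model for repeated measures that uses all available visits:

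- outcomes: the T2 and T3 values;
- covariates: the T1 value and recruitment source, which is the randomisation stratum;
- group, time and group-by-time, with unstructured covariance.

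Report the group difference at T2 and at T3. Keep the T2–T3 change comparison as a derived estimate from the same model, namely the T3 difference minus the T2 difference. The T3 difference is needed because a fully maintained benefit gives a T2–T3 contrast of zero: with −0.40 SD at both visits, −0.40 − (−0.40) = 0. The Assessments section would otherwise look to that contrast alone for a longer-term effect.

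Drop the data-driven switch and use robust or bootstrap standard errors if residuals are skewed.

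Cost: a change of wording, standard software, slightly more analysis work and no new data. The model relies on missing at random. People with neither T2 nor T3 still add nothing to it, so their number by group should be reported.

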### Trial registration and ethics approval

Ethical approval has been granted from the University of Melbourne Human Research and Ethics Committee (0824406). All participants will provide written informed consent. The trial is registered on the Australian and New Zealand Clinical Trials Registry (ACTRN12608000390381).

## Discussion

This randomized controlled trial will establish the outcomes and cost effectiveness of a short integrated rehabilitation program of home-based therapy for people with PD that integrates PRST**,** MST and falls education. Providing therapy in the home may enhance participation in the study and allow people with PD with a range of disabilities and levels of progression to access rehabilitation programs. The results will build on those from our earlier study [27]. This compared the ability of MST with falls education, and PRST with falls education to reduce falls each relative to a control group who received life skills education only. The results from the current project will provide further information on the effectiveness of home-based programs for people living with PD.

## Abbreviations

PD, Parkinson’s disease; H&Y, Hoehn and Yahr; MDS-UPDRS, Movement Disorders Society-Unified Parkinson’s Disease Rating Scale; PDQ-39, Parkinsons’ Disease Questionnaire – 39 items; EQ-5D, EuroQol-5D; mRPE, Modified rate of perceived exertion; IR, Integrated rehabilitation; LS, Life skills; MST, Movement strategy training; PRST, Progressive resistance strength training; ICER, Incremental cost effectiveness ratio.
